### Outcomes {12}

The primary outcome measure will be a change in the symptoms of anxiety and depression, as determined by the RCADS-25-P and RCADS-25-C [28, 29], between study entry (T0) and 1–3 days after the end of the intervention (T1, after five sessions of psychotherapy, five weeks of access to the psychoeducational videos, or both). The RCADS-25-P and RCADS-25-C will be completed by an independent clinician blinded to the allocation, on the basis of interviews (through videoconference or telephone call) with the guardians and the children/adolescents, respectively. The response variables will be the continuous T-scores for the three RCADS-25 domains (total, depression and anxiety).

Secondary outcomes will include the following: a change in the symptoms of anxiety and depression at follow-up; global functioning, assessed by the Clinical Global Impression (CGI) scale [41] and the Children’s Global Assessment Scale (CGAS) [30, 42]; the impact of mental health symptomatology, as determined with the Strengths and Difficulties Questionnaire (SDQ) impact supplement [43]; changes in irritability; emotional problems; environmental changes, as determined by passive smartphone data collection; the level of parental satisfaction with the telepsychotherapy sessions; and the potential harm (emergence of suicidal ideation and worsening of the quality of family relationships).

The blinded assessor will evaluate the difference between the anxiety and depressive symptomatology observed at T0 and that observed at follow-up (T2, 30 days after the last psychotherapy session, for the intervention group, or 30 days after the last video is made available, for the active control group) in an interview with the guardian and the child/adolescent, using the RCADS-25-P and RCADS-25-C.

The blinded assessor will evaluate the global functioning of the participants in interviews with the guardian and the child/adolescent (through videoconference or telephone call). The CGI-Severity (CGI-S) and CGAS scores obtained at T0 will be compared with those obtained at T1 and with those obtained at T2. Scores on the CGI-S range from 1 to 7, higher scores corresponding to greater symptom intensity. Scores on the CGAS range from 0 to 100, higher scores indicating better functionality. The CGI-Improvement (CGI-I) scores will be assessed at T1 and T2. Scores on the CGI-I range from 1 (“very much improved”) to 7 (“very much worse”).

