Participants ≥ 12 years of age with access to a smartphone will be asked to install an application designed to passively collect data from the smartphone sensors—the passive remote measurement technology (pRMT) application from the Remote Assessment of Disease and Relapse (RADAR)-base platform [47]. The pRMT application will run in the background, requiring minimal input from participants, and will use the smartphone sensors to collect data on the following: ambient noise and light; relative GPS location (i.e. the distance travelled, rather than absolute coordinates or precise geographical location); the number of Bluetooth-enabled devices nearby; the duration of calls; the number of text messages and emails; the time spent using the smartphone; the time spent on social media; and battery life. Passive data collection will take place from T0 to T2. The aim of these measures is to determine whether parameters such as physical activity (estimated by the distance travelled) and proximity to other people (estimated by analysing Bluetooth connectivity with other smartphones) might be related to changes in anxiety and depressive symptomatology and whether those parameters show any improvement after the trial.

To assess the level of parental satisfaction with the telepsychotherapy sessions (intervention group only), parents will be asked to complete an adapted version of the Telemedicine Satisfaction Questionnaire (TSQ) [48].

Potential harms were defined as the emergence of suicidal ideation and worsening of the quality of family relationships. As previously mentioned, we will use the parent-report four-item MFQ-SI to assess suicidal ideation in the last 2 weeks [31, 32], comparing T1 with T2. The MFQ-SI will be completed by the blinded assessor in an interview with the guardian (through videoconference or telephone call). To identify worsening of the quality of family relationships in the last 2 weeks, we will use the family relationship subscale of the family impact module of the Pediatric Quality of Life Inventory (PedsQL) [49]. The PedsQL will be completed by the blinded assessor in interviews with the guardian at T0, T1 and T2. The family relationship subscale of the PedsQL comprises five items, covering topics such as “lack of communication between people in my family”. For each item, there is a 5-point Likert scale (responses ranging from “never” to “almost always”).

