### Adverse event reporting and harms {22}

The risk for participants is expected to be minimal, because the intervention is non-invasive. However, we will monitor participants to identify any potential side effects of the intervention, including increased symptomatology and emergence of suicidal ideation. In the clinical assessments (interviews with the guardians and the children/adolescents), the blinded assessor will collect data on symptomatology (through the use of the RCADS-25-P, ARI, SDQ impact supplement, CGI-S and CGI-I), emergence of suicidal ideation (through the use of the MFQ-SI) and disruption of family dynamics (through the use of the PedsQL family impact module). The blinded assessor will also collect data on any other form of mental health treatment that the family seeks between T0 and T2, including psychotherapy with other providers or psychopharmacological treatment.

If by the end of treatment the assessor identifies a significant level of symptomatology, the child/adolescent will be referred to continue the treatment within the Brazilian public health care system. One of the child psychiatrists on the team will evaluate the child/adolescent if necessary.

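### Suicidal ideation is asked about for the last 2 weeks only, at T1 and T2, which leaves roughly half of T0–T2 outside structured questioning in either arm

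*Protocol article*

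**What the plan says.** Outcomes {12} defines two potential harms: emergence of suicidal ideation and worsening of family relationships.

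- **Ideation:** "we will use the parent-report four-item MFQ-SI to assess suicidal ideation in the last 2 weeks", with the comparison given as "comparing T1 with T2".
- **Family relationships:** the same look-back applies ("To identify worsening of the quality of family relationships in the last 2 weeks"), using a PedsQL subscale. "The PedsQL will be completed by the blinded assessor in interviews with the guardian at T0, T1 and T2".
- **Timing of T1:** the primary outcome is measured "between study entry (T0) and 1–3 days after the end of the intervention", that is, "after five sessions of psychotherapy, five weeks of access to the psychoeducational videos, or both".
- **Timing of T2:** the same section sets it at 30 days after the last session (intervention) or 30 days after release of the last video (control).

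Intervention description {11a} plans five weekly sessions and releases the last two videos in the fourth week. Criteria for discontinuing or modifying allocated interventions {11b} caps the time from first to last session at 4 weeks.

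Adverse event reporting and harms {22} promises that "we will monitor participants to identify any potential side effects of the intervention, including increased symptomatology and emergence of suicidal ideation". It names the MFQ-SI, at the clinical assessments, as the tool for ideation.

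**The concern.** Emergence is something that happens over a period. A 2-week look-back at two visits records whether ideation was present recently. If each interval between visits were about 2 weeks, the two would nearly coincide. Most of the intervals here are longer, so a child could develop ideation early in treatment, recover, and be recorded as free of it at both visits. On the weekly schedule, the T1 window opens after session 3 in the intervention arm and in the fourth week of video access in the control arm.

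At stake is the safety statement. A low count at T1 and T2 could be read as few cases over the trial, when it describes only the 2 weeks before each interview.

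**Working it through.** The protocol gives no coverage figure, so there is none to reproduce. The check is a day count.

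**Inputs.** Day 0 is session 1 (intervention) or the start of video access (control).
- Look-back: 14 days (Outcomes {12}).
- Last session: day 28 (weekly sessions {11a}; 4-week cap {11b}).
- Control access before T1: 35 days (Outcomes {12}).
- T1: 1–3 days after the end of the intervention (Outcomes {12}).
- Last video: fourth week, day 21–27 ({11a}).
- Gap from T0 to day 0: not stated. Assumed 0, 7 or 14 days; the EMA week before the intervention in Participant timeline {13} suggests about 7.

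**Visit days**

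| | Intervention | Control |
|---|---|---|
| T1 | 28 + 1 to 3 = day 29–31 | 35 + 1 to 3 = day 36–38 |
| T2 | 28 + 30 = day 58 | 21 to 27 + 30 = day 51–57 |
| T1–T2 | 58 − 31 to 58 − 29 = 27–29 days | 51 − 38 to 57 − 36 = 13–21 days |

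**Covered share of start to T1.** Intervention: 14/31 to 14/29 = 45–48%. Control: 14/38 to 14/36 = 37–39%.

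**Share of T0–T2 outside both windows** = 1 − [min(14, T0–T1) + min(14, T1–T2)] / (T0–T2).

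| Gap T0 to start | Intervention | Control |
|---|---|---|
| 0 days | 30/58 = 52% | 23/51 to 29/57 = 45–51% |
| 7 days | 37/65 = 57% | 30/58 to 36/64 = 52–56% |
| 14 days | 44/72 = 61% | 37/65 to 43/71 = 57–61% |

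**Two sensitivity checks, gap 0, intervention arm**
- If T1 waits for five full weeks of video access as well as the sessions, T1 moves to day 36–38 but T2 stays at day 58. The uncovered share is still 30/58 = 52%.
- If sessions are compressed to the 48-hour minimum, the last session is on day 8, T1 on day 9 and T2 on day 38. The uncovered share is 15/38 = 39%. This is an extreme; the planned schedule is weekly.

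**What is missed.** Suppose an episode lasts *d* days and starts at a random time in an interval of *L* days. The share seen at T1 is about min(1, (14 + *d*)/*L*). The length *d* is an assumption.

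| *d* | Intervention, *L* = 31 | Control, *L* = 38 |
|---|---|---|
| 3 | 17/31 = 55% | 17/38 = 45% |
| 7 | 21/31 = 68% | 21/38 = 55% |
| 14 | 28/31 = 90% | 28/38 = 74% |

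**Does this bias the arm comparison?** With a common onset rate *r* per day, an interval of *L* days produces *rL* episodes. The expected number seen at T1 is *rL* × (14 + *d*)/*L* = *r*(14 + *d*). *L* cancels, so the arms have equal expected counts. The lower control percentages reflect a longer interval that generates more episodes.

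**Does anything else in the document fill the gap?**
- Plans for assessment and collection of outcomes {18a} says that the RCADS-25 does not cover suicidal ideation.
- The EMA is limited to participants aged 12 or over with a smartphone, is optional, runs only before and after the intervention, and has no ideation item in Table 1.
- Other mental health treatment is recorded for all of T0–T2, but that captures help-seeking.
- The CGI-I is a global rating.

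**The case against.** The strongest defence has three parts.

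1. **The 2-week window belongs to the scale as the protocol uses it.** Eligibility criteria {10} applies the same window at entry, and the protocol nowhere claims cumulative incidence over treatment. This stands as a reason to keep the standard scale for scoring. It does not make that scale a measure of emergence.
2. **Other routes exist.** Emerging ideation leads to referral under {11b}, adverse events go to the steering and ethics committees, and a condensed article may leave their collection to the full protocol. This stands in part: it would be too strong to say that ideation between visits can never come to light. But the look-back is stated here, {22} relies on the same instrument, and weekly therapist contact exists in one arm only.
3. **Longer recall is less accurate.** True, and it is the cost of the fix.

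A reader might also infer stronger points that the documents do not support:
- **That ascertainment is biased between arms.** Under equal daily risk the expected counts at T1 are equal, as shown above. Coverage also runs in opposite directions: lower in controls up to T1, but higher from T1 to T2 (67–100%, against 48–52% in the intervention arm).
- **That both intervals last 4 to 5 weeks.** Control T1–T2 is about 2 to 3 weeks, and T0–T1 can exceed 5 weeks.
- **That the early sessions are the ones most likely to disturb family relationships.** {11a} describes their aims as improving communication and coping with anger; nothing in it ranks sessions by risk.

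**Conclusion.** The point holds as under-ascertainment of suicidal ideation in both arms. About 45–61% of T0–T2 lies outside the two windows, given weekly sessions, the stated visit anchors and an assumed T0-to-start gap of 0–14 days. Compressed sessions could bring the intervention figure down to about 39%. How many episodes are missed depends on their length, which the documents do not give.

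The PedsQL subscale has the same window, but its items are frequency ratings without a date of onset, so the remedy for ideation does not carry over. Correct labelling is enough there. This is a cheap improvement to safety ascertainment; the efficacy analysis is unaffected.

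**What to change.** - Keep the 2-week MFQ-SI and PedsQL subscale at their scheduled visits as the scored measures.
- At T1 and T2, have the blinded assessor also ask the MFQ-SI ideation items once for any time since the last interview, with an approximate date.
- Define new ideation against the answers held at T0. The item on thoughts of killing oneself is already unendorsed at entry, because {10} excludes children whose parent endorses it.
- Report new ideation by arm with days of exposure, as a rate per person-time or over a window common to both arms. Raw counts would mislead: at interval midpoints, controls have 37/30 = 1.23 times the exposure up to T1 and 17/28 = 0.61 times from T1 to T2.
- Leave the PedsQL subscale unchanged and label it as covering the 2 weeks before each visit.

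The cost is a few questions in interviews already scheduled, a form amendment, and less accurate recall over the longer period. If the interviews are already complete, report ideation as present in the 2 weeks before T1 or T2, and state the share of follow-up covered in each arm.

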Participants will be excluded if there has been no contact between the child/adolescent and the guardian in the 15 days preceding the intervention; if there is not at least one parent/guardian participating in each session (intervention group) or available to watch the videos along with the child/adolescent (active control group); if the guardian is unable to understand the scales used in the assessments or the content of the interventions, according to the judgement of a clinical psychologist; or if the child/adolescent has previously been diagnosed with an autism spectrum disorder, schizophrenia or intellectual disability or has clinical signs of a severe mental disorder or social condition that requires more intensive assessment and treatment, such as severe mood disorder, suicide risk, intense intra-familiar conflict or intense maltreatment victimisation, according to the judgement of a clinical psychologist. Suicidality will be assessed with the aid of the parent-report four-item composite version of the Mood and Feelings Questionnaire for Suicidal Ideation (MFQ-SI) [31, 32], which comprises the following items (marked as “not true”, “sometimes true” or “true”, in relation to the last two weeks): “S/he thought that life wasn’t worth living”; “S/he thought about death or dying”; “S/he thought his/her family would be better off without him/her”; and “S/he thought about killing him/herself”. Children and adolescents whose parents marked the final statement as “true” or “sometimes true” will be excluded from the study and referred for appropriate care that is more intensive. Individuals who have been treated with any psychiatric medication or psychotherapy in the last 30 days will also be excluded.

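### Emergence of suicidal ideation is compared from T1 to T2, after treatment has ended, so onset during treatment shows as no change or as improvement in the stated contrast

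*Protocol article*

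**What the plan says.** All references are to the protocol article.

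- **The harm.** Outcomes {12} lists among the secondary outcomes "the potential harm (emergence of suicidal ideation and worsening of the quality of family relationships", and later repeats the definition: "Potential harms were defined as the emergence of suicidal ideation and worsening of the quality of family relationships".
- **The comparison.** The same section says the parent-report four-item MFQ-SI will be used "to assess suicidal ideation in the last 2 weeks [31, 32], comparing T1 with T2". No section states a comparison of the MFQ-SI with T0.
- **The time points.** The primary outcome runs "between study entry (T0) and 1–3 days after the end of the intervention (T1, after five sessions of psychotherapy". The follow-up visit is "T2, 30 days after the last psychotherapy session, for the intervention group, or 30 days after the last video is made available".
- **Use at entry.** Eligibility criteria {10}: "Suicidality will be assessed with the aid of the parent-report four-item composite version of the Mood and Feelings Questionnaire for Suicidal Ideation (MFQ-SI". The exclusion rule rests on the last of the four items: "Children and adolescents whose parents marked the final statement as “true” or “sometimes true” will be excluded from the study". The other three items do not trigger exclusion under that rule.
- **The other harm.** For family relationships, Outcomes {12} says: "The PedsQL will be completed by the blinded assessor in interviews with the guardian at T0, T1 and T2".
- **Safety monitoring.** Adverse event reporting and harms {22} says the blinded assessor will use the MFQ-SI to pick up emerging suicidal ideation among possible side effects of the intervention. It names no time contrast.

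**The concern.** Emergence means that something absent before is present now, so it needs a reference point before the exposure. Here the reference point is T1, when the exposure is over. An analyst who follows the sentence as written would estimate what happens to ideation in the weeks after treatment, not whether it arose while treatment was given.

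The error also has a direction. A child whose ideation starts during the programme is already positive at T1. From there the T1-to-T2 change can only be flat or show improvement, unless the child worsens further. An arm with more onset during treatment therefore has more room to look better at T2. At stake is one of the two harms the protocol defines, in children and adolescents selected for high anxiety and depression scores.

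**Working it through.** The protocol gives no figure for this outcome, so there is none to reproduce. The sample size calculation plays no part in the point. The check sets the sections side by side, then works through the algebra of the contrast.

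**1. Where the interval lies.** T0 is study entry. T1 follows the end of treatment by one to three days. In the intervention arm T2 is 30 days after the last session, so T1 to T2 spans 30 − 3 = 27 to 30 − 1 = 29 days, all after treatment. In the control arm T1 follows five weeks of video access, so T1 to T2 again excludes the treatment period.

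**2. How the other outcomes are referenced (Outcomes {12}).**

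| Measure | Stated time points |
|---|---|
| RCADS-25, parent and child | T0 with T1 (primary); T0 with T2 (secondary) |
| CGI-S, CGAS | T0 with T1; T0 with T2 |
| SDQ impact | T0 with T1; T0 with T2 |
| ARI | T0 with T1; T0 with T2 |
| PedsQL family relationships (the other harm) | collected at T0, T1 and T2 |
| **MFQ-SI** | **T1 with T2** |

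CGI-I is taken at T1 and T2 only, but it is itself a rating of change. Among the measures compared over time, only the MFQ-SI has a stated comparison that leaves out T0.

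**3. What the contrast estimates.** Let pI1 and pI2 be the proportions positive on the final item in the intervention arm at T1 and T2, and pC1 and pC2 those in the control arm. At T0 all are zero, because positive children are excluded. The excess in the intervention arm is e1 = pI1 − pC1 at T1 and e2 = pI2 − pC2 at T2.

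- T0-to-T1 contrast: (pI1 − 0) − (pC1 − 0) = e1
- T0-to-T2 contrast: (pI2 − 0) − (pC2 − 0) = e2
- T1-to-T2 contrast: (pI2 − pI1) − (pC2 − pC1) = e2 − e1

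The stated contrast subtracts the excess present at the end of treatment. If the excess persists (e2 = e1) it gives zero. If the excess shrinks (e2 < e1) it is negative and reads as benefit. This does not depend on the prevalences chosen. It also takes the favourable reading that the T1-to-T2 change is compared between arms, which the sentence does not say.

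**4. Illustration.** The prevalences are assumed, since the protocol gives none. Control is 4% at T1 and T2.

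| Intervention arm, T1 then T2 | T0–T1 | T0–T2 | T1–T2 (as stated) |
|---|---|---|---|
| Arises in treatment, resolves: 10%, 4% | 10 − 4 = +6 | 4 − 4 = 0 | (4 − 10) − (4 − 4) = −6 |
| Arises in treatment, persists: 10%, 10% | +6 | 10 − 4 = +6 | (10 − 10) − 0 = 0 |
| Arises after treatment: 4%, 10% | 0 | +6 | (10 − 4) − 0 = +6 |

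Entries in the last three columns are percentage points. Only the third pattern registers as harm.

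**5. Final item and other items.** For the final item, T0 is zero by design, so the T1 proportion by arm already measures emergence. The other three items may be positive at entry. A child positive on one of them at T1 may have been positive throughout, and only the T0 value separates persistence from emergence.

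**6. Recall.** The MFQ-SI looks back two weeks. At T1 it therefore reaches 14 − 3 = 11 to 14 − 1 = 13 days into the treatment period. Five weekly sessions span 4 × 7 = 28 days from first to last, so roughly the first half of that span is not covered at T1, whichever baseline is used.

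**The case against.** A reader might go further and infer that the trial cannot detect suicidal ideation arising during treatment, or that every onset between T0 and T1 is missed. The documents do not support that. The MFQ-SI has to be recorded at T1 for the stated comparison to be made. A positive final item there is new onset because of the entry exclusion, and a simple count by arm at T1 would show it. Individual cases can also be seen and referred: Criteria for discontinuing or modifying allocated interventions {11b} and Adverse event reporting and harms {22} both provide for this. The fault lies in the outcome comparison, not in the care of individual children. Nor does the absence of a data monitoring committee bear on which visits are compared.

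It can also be said that Statistical methods {20a} plans mixed models with arm and time, with marginal means extracted by both, so the analysis need not be a lone T1-to-T2 change. But that section does not name the MFQ-SI and supplies no T0 contrast for it. The harms section {22} is likewise silent on the contrast.

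The wording may be a slip, since the other measures compared over time use T0. That is plausible, but the published sentence would still need correcting.

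Two further cautions stand. First, that an assessor-collected MFQ-SI exists at T0 is an inference: the measure is used for eligibility, and Participant timeline {13} and Data management {19} say clinical data from screening are confirmed or corrected at baseline. The schedule figure, which would settle it, is not available here. Second, a T0-to-T1 contrast would still miss ideation that arose and resolved in the early weeks of treatment.

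**Conclusion.** The point holds as a mismatch between the defined harm and its stated comparison. The protocol defines the harm as emergence of suicidal ideation but compares T1 with T2, an interval wholly after treatment. Under that contrast, ideation that begins during treatment and persists contributes no change, and ideation that begins and resolves contributes apparent improvement.

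The size is the excess at the end of treatment, which the contrast subtracts in full. Under the assumed prevalences this turns +6 points into −6 or 0. The 6 points are illustrative; the subtraction is not.

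The conclusion rests on reading the sentence literally and, for the remedy, on an MFQ-SI value being available at T0. It does not extend to a claim that treatment-period onset goes unrecorded. The primary outcome and the sample size are unaffected.

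**What to change.** 1. In Outcomes {12}, replace the T1-with-T2 comparison for the MFQ-SI by comparisons of T0 with T1 and of T0 with T2, between arms, in line with the other outcomes.
2. Report by arm the proportion with new final-item ideation at T1 or T2, and the proportion whose four-item score has worsened from T0. Give a 95% confidence interval for each between-arm difference.
3. Reconcile Eligibility criteria {10}, Outcomes {12} and Adverse event reporting and harms {22}, so that all three describe the same measurement times and the same definition of emergence, and confirm that the MFQ-SI is recorded at T0.
4. State as a limitation that two-week recall means T1 captures only the last part of the treatment period.

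The cost is a sentence or two of text and a short harms table. If the T0 value is confirmed, no new measurement is needed. Sample size and clinical management do not change.
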